### 8.1.3

#### **Other study parameters**

- Patient characteristics (e.g. age, gender, BMI, ASA score, ethnicity, employment status, and education level).
- Surgical characteristics (e.g. surgical approach, prosthesis type and fixation method, surgical duration, and intra-operative complications)
- Postoperative characteristics (e.g. length of hospital stay, in-hospital complications and discharge destination)
- Healthcare consumption, complications, and surgical interventions from the time of THA/TKA up to one year postoperatively

## **8.2 Randomisation, blinding and treatment allocation**

Treatment allocation will occur naturally through the stepped-wedge design of the study. All participating centers will initially use routine follow-up (RFU) and will transition to check-up on demand (COD) at predetermined points during the study

## **8.3 Study procedures**

Patients scheduled for total THA or TKA will be invited to participate in the study prior to their surgery. This timing ensures that participation is not influenced by the surgery itself, and a patient's potential preference for follow-up care.

Information on patient background will be collected to explore potential differences in follow-up needs, including among patients with different ethnic backgrounds. Previous research shows that people with a migrant background visit specialists and hospitals less often than

native Dutch patients with similar health and SES (19). Acknowledging the sensitivity of this topic, a 'prefer not to say' option is provided.

If the center where the patient undergoes surgery is in RFU phase, follow-up visits will be scheduled within 3 months and 1 year postoperatively. If the center is in the COD phase, patients will receive instructions during their 3-month follow-up on when and how to contact a HCP in case of concerns or complaints. In the COD phase, no standard 1-year follow-up visit will be scheduled.

Participants will be followed up to 2 years after surgery, i.e. 1 year after RFU or COD. The primary outcome, costs and the EQ-5D-5L will be measured pre-operative, at 1 year after surgery and at 15, 18 and 24 months after surgery. The other outcomes will be measured pre-operative (baseline) and at 1 year and 2 years after surgery (endpoint). Figure 1 depicts a flowchart of study participation.

[figure not shown]

**Figure 1. Flowchart of study participation.**

All participants will be asked to complete the questionnaires online or on paper, this will take around 30 minutes. Table 2 shows which assessments will be made at which times during follow-up. Study data will be collected in the patient's electronic file and will finally be collected onto an electronic case report form (eCRF) in Castor EDC.

**Table 2. Overview of the study procedures and assessments at each time point.**

|                               | Before surgery | Surgery | Discharge | 3 months after surgery | 1 year* after surgery: RFU or COD | 15 months* after surgery | 18 months* after surgery | 24 months* after surgery |
|-------------------------------|----------------|---------|-----------|------------------------|-----------------------------------|--------------------------|--------------------------|--------------------------|
| ICF procedure                 | X              |         |           |                        |                                   |                          |                          |                          |
| Patient characteristics       | X              |         |           |                        |                                   |                          |                          |                          |
| Surgical characteristics      |                | X       |           |                        |                                   |                          |                          |                          |
| Postoperative characteristics |                |         | X         |                        |                                   |                          |                          |                          |
| Clinical visit                |                |         |           | X                      | X (for RFU)                       |                          |                          |                          |
| X-ray                         |                |         |           | X                      | X (for RFU)                       |                          |                          |                          |
| Complications                 |                |         |           |                        |                                   |                          |                          | X                        |
| Surgical interventions        |                |         |           |                        |                                   |                          |                          | X                        |
| Healthcare consumption        |                |         |           |                        |                                   |                          |                          | X                        |
| PROMIS                        | X              |         |           |                        | X                                 | X                        | X                        | X                        |
| EQ-5D-5L                      | X              |         |           |                        | X                                 | X                        | X                        | X                        |
| NPRS                          | X              |         |           |                        | X                                 |                          |                          | X                        |
| NSRS                          |                |         |           |                        | X                                 |                          |                          | X                        |
| Costs                         |                |         |           |                        |                                   | X                        | X                        | X                        |

**\*A maximum window of  $\pm 30$  days will be applied for data collection of the questionnaires.**

*PROMIS physical function* will be obtained using computer-adaptive testing (CAT). If this is not feasible, the short form (SF) can be completed either digitally or on paper. Version 10a will be used. The SF PROMIS physical function consists of 10 questions and is expressed by raw summed score ranging from 10 to 50, which can be converted to a T-score and SE. The T-score is a standardized score with a mean of 50 and a SD of 10.

*Health related quality of life (EQ-5D-5L)* is a general health-related quality of life questionnaire and consists of five questions regarding mobility, self-care, usual activities, pain/discomfort and anxiety/depression and one visual analog scale (VAS) to document the perceived quality of life. The quality of life is described by 2 scores, the index value, which range from 0 to 1, and the VAS score, which range from 0 to 100. For both scores applies the higher the better.

*Numeric Rating Scale for pain (NPRS)* is a scale ranging from zero to ten on which patients can score their pain. It is a widely used instrument in varying populations due to its ease of administration and clinical relevance to the patient. The lower the score, the better.

*Numeric Rating Scale for satisfaction (NSRS)* will be measured by a single question: “How satisfied are you with the results of the treatment?” The patient will answer this question with a NRS scale ranging from zero to ten. The higher the score, the better.

*Health consumption and costs* will be measured using the EPD. Health consumption includes both the primary outcomes clinical visits and X-rays, as well as additional health care use, including telephone consultations and scans. The LROI register will be used to collect data about revision surgery. A questionnaire will be used to get more insight in the health consumption and costs which cannot be obtained from the EPD. This questionnaire is made in collaboration with a HTA expert and patient representatives.

### **8.4 Withdrawal of individual research participants**

Participants can leave the study at any time for any reason without any consequences if they wish to do so. The investigator can decide to withdraw a participant from the study for urgent medical reasons.

### **8.5 Replacement of individual research participants after withdrawal**

Replacement of individual subjects after withdrawal is not applicable, as the power calculation has already accounted for potential loss to follow-up.

### **8.6 Follow-up of research participants withdrawn from treatment**

If a participant chooses to withdraw from the study, all data collected up to the point of withdrawal may still be used for analysis, unless the participant explicitly requests otherwise.

### **8.7 Premature termination of the study**

As both COD and RFU are part of standard care, premature study termination is not expected unless significant safety concerns arise. If the study is terminated early, subjects will continue follow-up according to the standard care procedures at their hospital. Subjects will not face any additional risks if the study is prematurely terminated. All relevant parties will be notified, and data collected up until termination will be securely managed and analyzed. A final report outlining the reasons for termination and the findings will be provided to the relevant stakeholders.

## **9. SAFETY REPORTING**

### **9.1 Temporary halt for reasons of research participant safety**

In accordance to section 10, subsection 4, of the WMO, the sponsor will suspend the study if there is sufficient ground that continuation of the study will jeopardise participant health or safety. The sponsor will notify the review committee without undue delay of a temporary halt including the reason for such an action. The study will be suspended pending a further positive decision by the review committee. The investigator will take care that all participants are kept informed.

### **9.2 AEs, SAEs**

#### **9.2.1**

##### **Adverse events (AEs)**

Adverse events are defined as any undesirable experience occurring to a participant during the study. In this study, complications, surgical interventions, and healthcare use are systematically collected as part of the study outcomes and are therefore already recorded. As such, these do not need to be reported separately as adverse events. Only events that can be directly linked to the presence or absence of the clinical visit and X-ray 1 year after surgery should be reported as adverse events.

#### **9.2.2**

##### **Serious adverse events (SAEs)**

A serious adverse event is any untoward medical occurrence or effect that

- results in death;
- is life threatening (at the time of the event);
- requires hospitalisation or prolongation of existing inpatients' hospitalisation;
- results in persistent or significant disability or incapacity;
- is a congenital anomaly or birth defect; or
- any other important medical event that did not result in any of the outcomes listed above due to medical or surgical intervention but could have been based upon appropriate judgement by the investigator.

Only events that are related to the study procedures (RFU or COD) will be considered as serious adverse events. An elective hospital admission will not be considered as a serious adverse event.

Due to the low risk of the interventions (COD or RFU), which are both already part of standard care, hardly any SAEs are to be expected. This means all (S)AEs related to

participation in this study protocol, meaning from COD and RFU, will not be reported to the METC, as no patient benefit is expected from this.

## **10. STATISTICAL ANALYSIS**

All analyses will be performed separated for THA and TKA and will be performed using SPSS or R. Categorical data will be presented as numbers and percentages. Continuous variables will be presented by mean and standard deviation in case of a normal distribution. In case of non-normality, median and interquartile range will be given.

Missing data will be minimized as much as possible by contacting patients in case of incomplete questionnaires. After finalizing the database, the extent of missing data will be assessed. Mixed models will address missing data, and if necessary, multiple imputation will be employed, provided that the data are missing at random (20,21).

### **10.1 Primary study parameter(s)**

PROMIS physical function will be presented as mean with standard deviation, assuming normality. Differences in PROMIS physical function between the RFU and COD groups will be compared using linear mixed models, with repeated measurements clustered within participants and participants clustered within hospitals (random intercepts). The intervention group (RFU vs. COD), baseline PROMIS physical function, and time points (12, 15, 18 and 24) will be included as fixed effects to determine the crude effect of the intervention at each time point, with the primary outcome at 24 months. Given the stepped wedge design, the duration of the intervention period differs between sites. Therefore “period” is also included as a fixed effect. To assess of the effect of COD might increase over a longer period of time, an interaction term (period \* intervention) will be tested for these possible time effects for the primary outcome.

For healthcare consumption, the percentage of patients who have had at least one clinical visit or X-ray 1 year after RFU or COD will be presented for each group. Additionally, the average number of visits and X-rays per patient will be reported.

A logistic generalized linear mixed model (GLMM) will be used to compare the presence or absence of visits/X-rays (yes/no per patient) between RFU and COD. A Poisson regression analysis will be performed to assess the average number of visits and X-rays per patient, adjusting for potential confounders. Interaction terms between the confounders and the intervention group will also be included to explore whether certain patient characteristics influence the differences in healthcare consumption between RFU and COD.

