### **4.4 Sample size calculation**

We carefully considered the number of patients needed to obtain reliable estimates of the outcomes with the co-creating stakeholders and also asked orthopaedic surgeons for their opinion of convincing evidence. The agreed sample size is 250 patients per group. To provide a rough indication of the statistical power, we used the online power calculator tool available on Sealed Envelope (18). If there is truly no difference between COD and RFU, 190 patients (per intervention group) are required to be 90% sure that the lower limit of a one-sided 97.5% confidence interval will be above the non-inferiority limit of 3 on the PROMIS score with a standard deviation of 9. Anticipating 20-25% loss to follow up, we will include 250 patients per study intervention group (RFU and COD), thus a total of 500 THA and 500 TKA patients.

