### **10.2 Secondary study parameter(s)**

For complications, surgical interventions, and additional healthcare consumption, the percentage of patients who have experienced each will be presented for each group.

Additionally, the total number of complications, interventions, and additional healthcare consumption per patient will be reported. Logistic GLMM will be used to compare the presence or absence of complications, surgical interventions, and additional healthcare consumption (yes/no per patient) between RFU and COD. A Poisson regression analysis will be performed to assess the total number of complications, interventions, and additional healthcare consumption per patient, adjusting for potential confounders.

Quality of life (EQ-5D-5L) and pain (NPRS) will be analysed using mixed models, with repeated measures clustered within participants and participants within hospitals (random intercepts). Intervention group (RFU vs. active COD vs. passive COD), baseline score, and time (15, 18 and 24 months) are included as fixed effects. Satisfaction (NSRS) will be analyzed using independent t test to compare the mean difference between the RFU and COD group.

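### The random-intercept model for PROMIS implies one variance and one within-patient correlation over four unequally spaced visits; the effect on the 24-month result is small, and the remedy is cheap

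*Protocol*

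**What the plan says.** Protocol 10.1 compares the groups on PROMIS physical function with a linear mixed model, "with repeated measurements clustered within participants and participants clustered within hospitals (random intercepts"). Intervention, baseline score and "time points (12, 15, 18 and 24) will be included as fixed effects", to give the intervention effect at each visit, "with the primary outcome at 24 months". Period "is also included as a fixed effect". No random slope, residual covariance structure, visit-specific variance or robust standard error is named.

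Protocol 10.2 uses the same structure for EQ-5D-5L and NPRS, "with repeated measures clustered within participants and participants within hospitals (random intercepts").

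Protocol 4.4 sizes the trial on a one-sided 97.5% confidence limit against a "non-inferiority limit of 3 on the PROMIS score with a standard deviation of 9". That is a single SD, not one per visit. It continues: "Anticipating 20-25% loss to follow up, we will include 250 patients per study intervention group (RFU and COD"), for each joint. The opening of section 10 leaves missing data to the mixed model, with multiple imputation if needed and if the data are missing at random.

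**The concern.** A participant intercept, a hospital intercept and independent residuals together fix the covariance of a patient's four scores. Every visit has the same variance, and scores 12 months apart correlate exactly as strongly as scores 3 months apart. Correlation between physical function scores normally weakens as the gap grows, and the SD need not stay constant during the second year.

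For an effect averaged over visits this would hardly matter. The primary effect is for 24 months alone, so its standard error depends on the 24-month variance, while this model pools the variance over all four visits. The non-inferiority decision rests on a confidence limit built from that standard error. The same covariance determines how earlier scores stand in for missing 24-month scores, so a wrong structure can also move the estimate.

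**Working it through.** **1. The plan's own figure.** Inputs from 4.4: margin 3, SD 9, true difference 0, one-sided 0.025, power 90%.

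n = 2 × SD² × (z₀.₉₇₅ + z₀.₉₀)² / margin² = 2 × 81 × (1.960 + 1.282)² / 9 ≈ 189.1, so 190 per group, as stated. Inflation: 190/0.80 = 238, 190/0.76 = 250, 190/0.75 = 254. The 250 per group therefore corresponds to 24% loss. This calculation contains no repeated measurements, so the point below does not change it.

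**2. What the stated model implies.** With variances σ²h (hospital), σ²p (participant) and σ²e (independent residual), the variance at every visit is σ²h + σ²p + σ²e. The correlation between any two visits is (σ²h + σ²p) / (σ²h + σ²p + σ²e), whatever the gap. For contrast, if the 3-month correlation were 0.85 and decayed with time, the 12-to-24-month correlation would be 0.85⁴ = 0.52.

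**3. Size on the planned design.** From the protocol: the Table 1 layout, 10 hospitals, 50 patients per hospital per joint, period as a fixed effect. Assumed: monthly periods (13 dummies), hospital ICC 0.02, decaying correlation as in step 2, 22.5% missing at 24 months, and an intervention-by-visit term, since 10.1 wants an effect at each visit. The model SE is what the random-intercept fit would report. The true SE is the sandwich value under the assumed covariance. One-sided error = Φ(−1.96 × model SE / true SE).

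| SD from 12 to 24 months | Model SE | True SE | Ratio | One-sided error |
|---|---|---|---|---|
| constant 9 | 2.473 | 2.482 | 0.996 | 2.54% |
| 8 to 10 | 2.414 | 2.465 | 0.979 | 2.75% |
| 10 to 8 | 2.539 | 2.508 | 1.012 | 2.36% |
| 7 to 11 | 2.361 | 2.458 | 0.960 | 2.99% |
| 11 to 7 | 2.609 | 2.542 | 1.026 | 2.22% |

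Example, SD 8 to 10: 2.414/2.465 = 0.979; Φ(−1.96 × 0.979) = Φ(−1.919) = 0.0275. Only the ratios matter here, because the absolute values depend on the assumed period length and ICC.

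A second set of assumptions took the correlation from 0.85 at 3 months to 0.60 at 12 months, with cumulative losses of 10%, 17% and 25%. It gave ratios of 0.994 (constant SD), 0.990 (8.5 to 9.5) and 0.986 (8 to 10), with errors of 2.57%, 2.61% and 2.66%. With two-month periods, or an ICC anywhere from 0 to 0.05, the error never exceeded 2.72%.

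**4. Is loss to follow-up the cause?** The step 3 calculation with no missing data gives 1.000 (constant SD), 0.985 (8 to 10) and 1.014 (10 to 8). With loss the ratios are 0.996, 0.979 and 1.012. Most of the standard-error misfit is already there with complete data, and it follows the change in SD.

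**5. Where loss does matter: bias.** Dropout was made to depend on the last observed score in opposite directions in the two arms, with constant SD 9.
- A plain two-group simulation (250 per arm, about 22% missing) gave a 24-month bias of −0.29 points with random intercepts and +0.05 with an unstructured covariance.
- On the Table 1 layout the two fits differed by 0.43 points (Monte Carlo SE 0.035), and 0.43/3 = 14% of the margin.
- Across the scenarios tried, the bias was about 0.1-0.5 points, or 3-17% of the margin. Its sign depends on which patients leave which arm.
- It was essentially nil when dropout did not differ by arm. It was also nil (−0.004) in a stepped-wedge run with arm-opposed dropout and SD rising from 8 to 10.

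**6. Treatment main effect only.** Without an intervention-by-visit term the ratio is 0.998-1.001 in every pattern. Such a model would not yield the 24-month effect that 10.1 asks for.

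**The case against.** The strongest reply is that residual covariance is the sort of detail a protocol leaves to the SAP, and 12.1 says there is one. Random intercepts describe the clustering. The protocol does not say that residuals are independent, and a residual structure can be added to a random-intercept model. This stands in part: the protocol does not rule out a richer structure. But it does state a model, and read in the ordinary way that model has the covariance in step 2. The point criticises a stated method and is not a complaint about an omission.

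The second reply is that the effect is trivial on this design. For the standard error that largely stands. Once period is in the model, the comparison between calendar periods dominates the uncertainty, and the within-patient covariance matters little.

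The third reply is that multiple imputation is available. It should remove most of the bias route if its models let each visit relate differently to the others. But it is conditional in section 10, and it leaves the standard-error misfit, which is present with complete data.

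A reader might infer something stronger. A plain two-group calculation with rising SD puts the 24-month standard error 8-13% too low and the one-sided error at 3.6-4.4%, and it is tempting to blame the 20-25% loss. The documents do not support this. The trial is a stepped wedge with period in the model, nothing says that the SD rises between 12 and 24 months, and a falling SD reverses the direction.

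**Conclusion.** The point holds as a minor one. The model as written, with independent residuals, has a covariance that is unlikely to suit visits at 12, 15, 18 and 24 months. On the planned layout the 24-month standard error is off by about 0-2%, and by 2.6-4% only for an SD shift of 4 points over the year. The one-sided error lies between about 2.4% and 2.75% for an SD shift of 2 points, and between 2.2% and 3.0% for the larger shift. It may be conservative or anti-conservative, and changing variance drives it more than loss does. This is not a serious type I error problem.

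Loss matters through a possible bias of roughly 0.1-0.5 points against the margin of 3, and only if score-dependent dropout differs between the arms.

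All correlations, visit SDs, dropout mechanisms, the ICC and the period length are assumptions. The protocol supplies only the single SD of 9, the loss range, the visit times and the layout.

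**What to change.** In 10.1, replace the participant random intercept with an unstructured residual covariance over 12, 15, 18 and 24 months, and keep the hospital random effect. Name heterogeneous Toeplitz as the fallback if the model does not converge. Use the same approach for the repeated-measures models in 10.2, over the visits at which each scale is collected.

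Four visits need 4 × 5 / 2 = 10 covariance parameters, estimated from about 500 patients per joint. The three visits listed in 10.2 need 3 × 4 / 2 = 6.

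The cost is one sentence in each section. The structure can be fitted in SPSS or R, which section 10 already names, and the sample size is unchanged. The only downside is that the fallback may be needed.

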## 3. STUDY DESIGN

This study has been developed in collaboration with stakeholders, as part of the Zorgevaluatie & Gepast Gebruik (ZE&GG) program. The stakeholders include clinicians, general practitioners, physiotherapists, patient representatives, epidemiologists, a cost-effectiveness expert, health insurers, guideline developers, and implementation experts. During a co-creation phase, multiple meetings were held in which the diverse interests and expertise of these stakeholders were integrated into the study design. Their continued involvement will guide the study's progress and implementation throughout the project.

This is a hybrid effectiveness (de-)implementation trial type II (17), with a stepped-wedge cluster trial design. A total of 10 hospitals will transition from a period with RFU to a period with COD, with a wash-out period (transition) of 2 months. The aim is to gradually de-implement RFU, with all centers eventually using COD as the standard of care. The inclusion period will last 14 months, followed by a 2-year follow-up for each patient. The total duration of data collection will be from July 2025 (first patient inclusion) to August 2028 (last patient, last visit).

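### The hospital-level random intercept assumes equal correlation within and between months, so the PROMIS interval can be too narrow if that correlation fades; add a hospital-by-month random effect

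*Protocol*

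**What the plan says.** Section 3 describes a stepped wedge: "A total of 10 hospitals will transition from a period with RFU to a period with COD". In Table 1 two hospitals enter transition at each monthly step from November 2025 to March 2026. Each hospital includes at most 5 patients per joint per month, and section 10 analyses THA and TKA separately.

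Section 10.1 sets the primary linear mixed model. Repeated measurements are clustered within participants, with "participants clustered within hospitals (random intercepts". Intervention, baseline PROMIS, time point and period are fixed effects, and a period-by-intervention interaction is tested. Section 10.2 gives the same two levels for EQ-5D-5L and NPRS, "participants within hospitals (random intercepts", and lists no period effect. No hospital-by-period term or decaying correlation is named in either section.

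The non-inferiority frame is in section 4.4 only: a "lower limit of a one-sided 97.5% confidence interval" set against a "non-inferiority limit of 3 on the PROMIS score with a standard deviation of 9".

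**The concern.** In a stepped wedge, much of the information on the intervention comes from comparing hospital-months under RFU with hospital-months under COD. Hospital conditions that shift from month to month therefore add noise to exactly that contrast. A single hospital intercept absorbs only the part of hospital variation that stays constant over the whole inclusion period. Any part that varies between months is treated as independent patient-level noise, and the standard error of the intervention effect comes out too small.

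The direction matters. A narrow interval puts the lower confidence limit too high, and for a non-inferiority limit that is the side on which a false claim is made. This is a stated choice of random effects, not a detail left open, and it rests on an equal-correlation assumption that the protocol does not justify.

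**Working it through.** **Stated sample size.** Under individual randomisation, n = 2 × 9² × (1.96 + 1.2816)² / 3² = 189.1, which rounds up to 190. This reproduces "190 patients (per intervention group) are required to be 90% sure". Dividing 190 by 0.76 gives 250, in line with "Anticipating 20-25% loss to follow up, we will include 250 patients per study intervention group". Neither step contains an ICC or a CAC, so both must be assumed below.

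**Inputs from the protocol.**
- Table 1 for one joint: 10 hospitals, 14 months, two hospitals per step, two transition months each. Monthly size is 2, 3, then 5, falling to 3 and 2 at the end. This gives 250 RFU and 250 COD patients, 50 per hospital.
- SD 9, so total variance 81.
- Loss to follow-up 22.5%, the middle of 20-25%.

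**Assumed.** ICC 0.01, 0.05 and 0.10; CAC 1, 0.8 and 0.5. The calculation uses the 24-month outcome without baseline adjustment.

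**Method.**
1. True covariance of two patients of one hospital: 81 × ICC in the same month, 81 × ICC × CAC in different months. Residual variance: 81 × (1 − ICC).
2. Planned model at hospital level: one intercept variance and one residual variance, with fixed months and intervention. Its variance components are set to the values to which REML converges under the truth in step 1.
3. With design matrix M, fitted covariance F and true covariance V, let A = (MᵀF⁻¹M)⁻¹. The model-based variance of the effect is the intervention element of A. The true variance is the same element of A MᵀF⁻¹ V F⁻¹M A.
4. R = true variance / model variance. One-sided error = 1 − Φ(1.96/√R).

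**Results, monthly periods.**

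| ICC | CAC | Model SE | True SE | R | One-sided error |
|---|---|---|---|---|---|
| 0.01 | 0.8 | 2.847 | 2.855 | 1.01 | 2.5% |
| 0.01 | 0.5 | 2.833 | 2.852 | 1.01 | 2.6% |
| 0.05 | 0.8 | 2.904 | 2.946 | 1.03 | 2.7% |
| 0.05 | 0.5 | 2.892 | 2.992 | 1.07 | 2.9% |
| 0.10 | 0.8 | 2.887 | 2.975 | 1.06 | 2.9% |
| 0.10 | 0.5 | 2.899 | 3.107 | 1.15 | 3.4% |

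At CAC 1, R is 1.00 and the error is 2.5% for every ICC. Worked example for the last row: 3.107² / 2.899² = 1.149; 1.96/√1.149 = 1.83; the upper tail is 3.4%.

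R − 1 is the excess of true over model variance. As a share of the true variance, 15% becomes 0.15/1.15 = 13%. In SE terms it is √1.15 = 1.07.

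**Simulation** (3,000 runs per scenario, 78% retained, z-based intervals, monthly periods, ICC 0.05). Coverage of the 95% interval was 0.952 at CAC 1, 0.939 at CAC 0.8 and 0.930 at CAC 0.5. One-sided error was 2.4%, 2.8% and 3.4%. The Monte Carlo error is about √(0.03 × 0.97/3000) = 0.3 percentage points, so this agrees with the table.

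**Longer periods.** From ICC 0.05, CAC 0.8 to ICC 0.10, CAC 0.5, R runs from 1.05 to 1.28 with two-month periods (error 2.8-4.1%) and from 1.06 to 1.33 with quarters (2.9-4.4%).

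**The case against.** Several points against the concern have weight.

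- A reader might infer that the intervals will be too narrow. The protocol does not support that. It gives no ICC or CAC, and at CAC 1 the planned model is exactly right. The narrowing is conditional.
- A reader might take the quarterly figures as the relevant ones because section 10.1 gives no period length. Table 1 heads its monthly rows as Period and moves hospitals at one-month steps, so the month is the only unit shown. The quarterly figures show sensitivity only.
- A reader might extend the fault to the logistic models for visits and X-rays, where a larger ICC is conceivable. Their random effects and their type of test are not stated, so the protocol cannot be said to fix the same structure there.
- The degrees-of-freedom method is ordinary SAP content, and its absence here is no error. It is worth settling in the same edit because there are only 10 hospitals.
- Section 10.1 itself describes a comparison and states no non-inferiority test. The link to the margin comes from section 4.4.
- The effect is modest beside the SE itself. About 2.9 in this layout compares with 9 × √(2/190) = 0.92 behind the stated sample size. That is a separate and larger matter, but correcting it would not correct the random effects.

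What stands is that sections 10.1 and 10.2 do name the structure for the linear models. In the scenarios computed, departures from equal correlation never made the interval too wide.

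**Conclusion.** The point holds in conditional form, as a change that should be made rather than one on which the trial depends. If within-hospital correlation falls between months, the planned linear models understate the variance of the intervention effect. With monthly periods and CAC 0.8 to 0.5, the true variance is about 3-7% above the model variance at ICC 0.05 and 6-15% above at ICC 0.10, and one-sided error is 2.7-3.4% against a nominal 2.5%. At ICC 0.01 it can be ignored; with longer periods it grows. The figures rest on assumed ICC and CAC, month-to-month correlation that drops once and then stays constant, SD 9, 22.5% loss and no baseline adjustment. The documents do not support a claim that the intervals are certainly too narrow, or that the logistic models share the fault.

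**What to change.** In the linear mixed models of sections 10.1 and 10.2, add a hospital-by-period random effect to the participant and hospital intercepts. Define period as the calendar month of inclusion in Table 1, as distinct from the measurement time point. Section 10.2 lists no fixed period effect, so add that with it. Use Kenward-Roger or Satterthwaite degrees of freedom for the 10 hospitals.

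For the logistic model of visits and X-rays, state the random effects and use the same structure where it can be estimated. Do not require it for rare complications or surgical interventions, where most hospital-months would have no event and the extra variance could hardly be estimated.

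The cost is a change of wording before analysis, slightly wider intervals and possible convergence problems with 10 hospitals. If the extra variance is estimated at zero, the model reduces to the planned one; state that fallback in advance.
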